# The efficacy of a health-related quality-of-life intervention during 48 weeks of biologic treatment of patients with moderate to severe psoriasis: study protocol for a multicenter randomized controlled trial

**DOI:** 10.1186/1745-6215-13-236

**Published:** 2012-12-08

**Keywords:** Dermatology, Randomized controlled trial, Patient-reported outcomes, Health-related quality of life, Intervention, Skindex-29, Psoriasis, Biologic, Etanercept

## Abstract

**Background:**

Interest in health-related quality of life (HRQoL) outcome research in dermatology is increasing, especially in the systemic treatment of psoriasis with biologic agents. In other specialties, such as oncology, the application of a HRQoL intervention is considered to be an aid for monitoring disease and treatment over time, for the communication with the patient, and for improving treatment outcome. However, in dermatology practice, the application of this intervention is relatively new. Moreover, evidence on the effectiveness of a HRQoL intervention in dermatology is missing. It is hypothesized that the application of a HRQoL intervention in dermatology practice will have a positive impact on patients’ HRQoL as well as on doctor-patient communication.

**Methods/design:**

In a prospective multicenter cluster randomized controlled trial, patients diagnosed with moderate to severe psoriasis who receive biologic treatment, will be followed for 48 weeks. The study sites, and not the patients, will be randomly allocated via a computer-based randomization system to either the intervention (treatment with etanercept and standardized HRQoL assessment and communication) or the control group (treatment with etanercept alone). The HRQoL intervention will include 1) the electronic assessment of the Skindex-29, a well-studied dermatology-specific HRQoL questionnaire, and 2) the communication of the resulting Skindex-29 data with the patient. Prior to study start, dermatologists in the intervention group will be educated and trained in standardized HRQoL assessment and communication using the Skindex-29. At six consecutive visits, patients at study sites in the intervention group will be asked to complete the Skindex-29 on a desk-top pc at the clinic, just before their consultation with the dermatologist. A print-out of the completed questionnaire will be made and, guided by this print-out, feedback on the HRQoL scores will be given during the consultation. Primary outcome parameters are the impact of the HRQoL intervention on patients’ HRQoL, and the effect of the HRQoL intervention on doctor-patient communication. Secondary outcomes include health status and disease severity.

**Trial registration:**

The Netherlands National Trial Register (NTR): NTR1364.

## Background

Patient-reported outcomes (PROs) are any aspect of a patient’s health status that comes directly from the patient without the interpretation of anyone other than the patient [1]. PROs provide information on the disease or treatment from a patient’s perspective. Examples of PROs are disease severity, general health status, adherence to treatment, satisfaction with treatment, and health-related quality of life (HRQoL). In accordance with the definition of the World Health Organization, HRQoL can be defined as a reflection of patients’ physical, psychological, and social functioning and well-being [2], and is generally considered as a key outcome parameter. Chronic skin diseases, such as psoriasis, are known to have a relatively high, negative impact on HRQoL [3]. As a result, interest in HRQoL outcome research in dermatology is increasing, especially in the systemic treatment of psoriasis with biologic agents.

Psoriasis is a systemic inflammatory skin disease with increased epidermal proliferation, affecting 2% of the population [4]. Common physical complaints of this chronic skin disease are skin soreness, burning sensations, itching, and joint pain. Therapies include topical treatments (for example, topical corticosteroids), photo(chemo)therapies (for example, UV-B and PUVA), and the conventional systemic treatments (for example, methotrexate and cyclosporin). For patients who fail or who are contraindicated or intolerant to these conventional treatments, biologic response modifiers, or biologics, are available, such as adalimumab, etanercept, infliximab, and ustekinumab. However, since dermatological treatment can only offer a temporary suppression or remission of symptoms, treatment efforts may increasingly be directed towards both a decrease of disease severity and an increase of a patient’s HRQoL.

Previous research, including studies in oncology, suggested that the application of a HRQoL intervention is considered to be an aid for monitoring disease and treatment over time, for the communication with the patient, and for improving treatment outcome [5,6]. However, in dermatology practice, the application of a HRQoL intervention is relatively new. Moreover, evidence on the effectiveness of a HRQoL intervention in dermatology is still missing. The present study may rectify this deficiency. It is hypothesized that a HRQoL intervention will significantly improve patients’ HRQoL, and will facilitate doctor-patient communication. In addition, this study offers the opportunity to examine the course of HRQoL during treatment, the mid- and long-term effects of treatment on HRQoL, and the relationship between disease severity and HRQoL during treatment.

**Figure 1 F1:**
[figure not shown]
**Clustered block randomization (a).** Clustering of the participating study sites (*N*=18). (**b**). Block randomization of the clustered study sites (*N*=18).

Since the intervention concerns both patients (for example, completion of the intervention questionnaire) and dermatologists (for example, providing feedback on the HRQoL scores of the intervention questionnaire), dermatologists in the intervention group will be educated and trained in standardized HRQoL assessment and communication prior to study start, during the ‘Intervention Training’ session on group level. The aim of this training is to enable dermatologists in the intervention group to adequately discuss HRQoL scores, as well as aspects of HRQoL, such as coping behavior and disease management. As a result, dermatologists will become more familiar and, thereby, comfortable with HRQoL assessment and communication in clinical practice. To this aim, the Intervention Training will include evidence-based background information on the construct HRQoL, its relevance to clinical practice, and the impact of psoriasis on HRQoL [5-10]. Dermatologists will be trained in the electronic assessment of the intervention questionnaire, the Skindex-29, and the interpretation of its scores. In addition, information on coping behavior and disease management will be provided.

In this study design neither the patients nor the dermatologists can be blinded to the intervention.

### Setting

The study will be conducted at 18 outpatient dermatology clinics in the Netherlands. Psoriasis patients will be consecutively invited to participate in the study after a medical decision is made to start biologic treatment with etanercept. Patients eligible for the study are diagnosed with a moderate to severe psoriasis (that is, a Psoriasis Area and Severity Index (PASI) of ≥8), and are 18 years or older at the time of informed consent. Patients who are mentally and/or physically unable to complete the study questionnaire(s), who speak the Dutch language insufficiently to fully understand and complete the intervention and/or study questionnaire(s), or who are not willing or not able to discuss HRQoL-issues, will be excluded from participation. A patient information form will be handed to all potential participating patients. Written informed consent needs to be obtained from all participating patients prior to study start.

This study is registered in the Dutch Trial Register (NTR1364). The study protocol has been reviewed and approved by the Competent Authority of The Netherlands (Centrale Commissie Mensgebonden Onderzoek - CCMO) (NL24494.018.08 BI), and reviewed by the Medical Ethics Committee of the Academic Medical Center, University of Amsterdam (EC AMC) (MEC 08/302). The EC AMC exempted this study for ethical approval. A written confirmation of this statement was given by the EC AMC (Ref: MEC 08/302# 08.17.1716; MEC 08/302# 08.17.1933). The study will be conducted in accordance with the applicable laws and regulations following the Declaration of Helsinki protocols.

### Participants

Psoriasis patients who will receive etanercept treatment by prescription from their dermatologists will be asked to participate in the study [11-14]. Thus, all included patients of both the intervention and control group will receive etanercept, as a constant factor, in accordance with routine clinical practice and, ideally, following the Dutch treatment guidelines for psoriasis: a PASI ≥8; ineffective or contra-indications to PUVA treatment twice weekly for 10 weeks; ineffective or contra-indications to treatment with cyclosporine 3-5 mg/kg/day for 16 weeks; and/or ineffective or contra-indications to treatment with methotrexate 22.5 mg/day for 16 weeks [15]. The per-protocol dose regimen of etanercept in week 0 to 12 (V1 to V3) is in accordance with the current Dutch summary of product characteristics (SmPC), namely: 2 x 50 mg/week. Depending on the PASI as measured at week 12 (V3), patients either discontinue treatment in case of PASI <50, or continue treatment during week 12 to 24 (V3 to V4). This treatment phase is called the induction phase. If PASI <75, patients will continue treatment with etanercept with 2 x 50 mg/week; if PASI ≥75, patients will continue with 2 x 25 or 1 x 50 mg/week. However, current clinical practice showed that a growing number of Dutch dermatologists continue treatment directly after the maximum treatment period of 24 weeks. Supporting evidence was found for an entire dosage regimen (week 0 to 48) in the British Association of Dermatologists Guidelines, in the German guidelines for systemic therapy, and in a study on the long-term safety and efficacy of 2 x 50 mg/week [16-19]. Per study protocol, patients will continue treatment during week 24 to 48 (V4 to V6), with 2 x 25 or 1 x 50 mg/week, which is called the maintenance phase (see Figure 2). The dosing schedule as suggested per protocol will be used as a guide for dermatologists. However, the actual dosing schedule to be given to patients will depend on routine clinical practice and the dermatologists’ prescriptions. Previous treatment with any biologic is allowed, taking the applicable wash-out period into account prior to treatment with etanercept. Concomitant topical treatment will be permitted.

**Figure 2 F2:**
[figure not shown]
Per-protocol dose regimen schedule for etanercept in the treatment of moderate to severe psoriasis.

### Intervention

The HRQoL intervention in this study consists of 1) the electronic assessment of the Skindex-29, a well-studied dermatology-specific HRQoL questionnaire, and 2) the communication of the resulting Skindex-29 data with the patient. The Skindex-29 consists of 29 questions, or items (for example items on pain, itch, embarrassment, frustration, social life, and interaction with others). Questions concern patients’ perception of the impact of the skin disease on aspects of HRQoL during the past week. These 29 items form three domains: symptoms, emotions, and functioning. Responses are given on a five-point response scale (ranging from ‘never’ to ‘all the time’), where scores are transformed to a 100-point scale, and domain and overall scores are being calculated by averaging responses to items in a given domain. Higher scores are indicating lower levels of HRQoL [20,21]. Several reviews suggested that the Skindex-29 is considered to be the instrument of choice in dermatology [9,22]

Before study start, dermatologists in the intervention group will be supported in the installation of the electronic version of the Skindex-29 on a desktop pc at the study sites, including a connection with a printer device. Prior to each consultation, patients in the intervention group will be asked to complete the Skindex-29 on a desk-top pc at the clinic. Patients will receive instructions from a dermatologist, or a designated representative, on how to complete this electronic questionnaire, without providing any information on the content or answers of the items. After completion, both the patient and the dermatologist will receive a print-out of the questionnaire, including the answers given and a matrix visually displaying the domain and overall scores. Guided by this print-out, the dermatologist will be able to systematically discuss the Skindex-29 answers and scores with the patient. In addition, and during consecutive consultations, the patient and the dermatologist will also be able to follow the HRQoL-scores over time as being displayed by this matrix showing repeated measurements.

The HRQoL intervention will be supported by patient information on quality-of-life, coping behavior, and disease management. At the first consultation, dermatologists will be instructed to provide two brochures to the patient; one with general information on HRQoL, and one on coping with and the management of psoriasis. At the second consultation, patients will receive another brochure about the treatment of psoriasis, including a chapter on HRQoL. In addition, a quality-of-life issue of a patient magazine from the Dutch Psoriasis Foundation will be provided to patients as well. At the third consultation, patients will receive a DVD on coping with psoriasis. At the fourth consultation, patients will receive a book entitled: ‘Psoriasis - Image, Experience, Treatment’, and patients will be instructed to read chapter 15: ‘The experience of psoriasis’. And, at the fifth consultation, patients will be asked to read chapter 16: ‘Coping with psoriasis’. Patients will be instructed to read and to watch the applicable patient information at home and prior to their subsequent consultation. The patient information can be stored in a study specific binder called ‘My Quality of Life’.

Additionally, all patients, both in the intervention and control group, will be asked to complete a diary to record the etanercept injections. These diaries will be used for monitoring the drug compliance.

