### Comparison

Patients in the control group will not receive the HRQoL intervention, but will receive etanercept treatment only. The consultation will be conducted according to routine clinical practice, or usual care. Dermatologists in the control group will be asked to stay naive to HRQoL assessment and communication during the course of this study; that is, they are not to implement electronic HRQoL assessment with and communication about the Skindex-29 during their consultations with study participants.

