The secondary efficacy endpoints include health status and disease severity. Health status will be measured with the Medical Outcomes Study 36-item Short-Form General Health Survey (SF-36), a well-established, eight-dimensional, generic HRQoL instrument [26,27]. The items represent issues relevant to health status, and relate to the past four weeks. The SF-36 will be completed at week 0 (V1), week 24 (V4), and week 48 (V6) by patients in both the intervention and control group. Disease severity will be measured with the PASI, the most widely used instrument for the measurement of the severity of psoriasis [28], and with an investigator global assessment (IGA) and a patient global assessment (PGA). The IGA is asking dermatologists: ‘In your opinion, how severe is your patient’s current skin condition?’, and the PGA is asking patients: ‘How severe is your current skin condition?’. Answers can be given on a five-point scale, ranging from ‘not severe’ to ‘very severe’. All patients will be asked to complete this set of questionnaires at the end of each patient consultation.

In addition, two evaluation questionnaires will be introduced to measure 1) aspects on satisfaction and 2) aspects on the feasibility of HRQoL assessment and communication in dermatology practice. First, at week 24 (V4) and week 48 (V6), an overall evaluation questionnaire will be handed to dermatologists in the intervention group, and to patients in both the intervention and the control group. This questionnaire comprises a study-specific questionnaire about 1) satisfaction with the treatment process, including doctor-patient communication, and 2) satisfaction with treatment outcomes. For example, ‘How satisfied are you about the conversations you have had with your doctor/patient?’. Answers are given on a VAS, ranging from ‘not at all satisfied’ to ‘very much satisfied’. Second, after each patient consultation, dermatologists in the intervention group will be asked to answer questions on aspects of feasibility, such as completion time, duration of the consultations, and (the number of) aspects of HRQoL discussed during the consultations. Dermatologist in the control group will only be asked about the duration of the consultations.

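### The IGA, and PASI if the same dermatologist scores it, is rated with the patient's Skindex-29 results known in the intervention arm only

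*Protocol article*

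**What the plan says.** The protocol article describes the visit as follows.

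- **Intervention section, timing.** "Prior to each consultation, patients in the intervention group will be asked to complete the Skindex-29 on a desk-top pc at the clinic".
- **Intervention section, who sees the result.** "After completion, both the patient and the dermatologist will receive a print-out of the questionnaire". The print-out shows the patient's answers with domain and overall scores and, at later visits, their course over time.
- **Intervention section, content.** "These 29 items form three domains: symptoms, emotions, and functioning".
- **Comparison section.** Of control dermatologists: "they are not to implement electronic HRQoL assessment with and communication about the Skindex-29 during their consultations with study participants".
- **Outcome measures.** Disease severity is a secondary efficacy endpoint, measured by PASI, IGA and PGA. The IGA asks dermatologists for their opinion of the current severity of the skin condition. No assessor is named for PASI. The account of these measures closes with: "All patients will be asked to complete this set of questionnaires at the end of each patient consultation".
- **Design of the study.** "neither the patients nor the dermatologists can be blinded to the intervention". The Discussion repeats this as a general threat to internal validity. It does not connect it with the severity ratings.
- **Background.** The relationship between severity and HRQoL during treatment is named as something the study can examine.

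**The concern.** Two kinds of unblinding should be kept apart. One is knowing the arm, which cannot be avoided here and is acknowledged. The other is holding this patient's own answers on symptoms, emotions and functioning when judging severity. The second exists in the intervention arm only, and it depends on nothing more than the order of steps within the visit.

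The IGA is a global opinion on a five-point scale, the kind of rating that freshly read patient reports can move. Sites are randomised, so raters are nested within arms. A shift caused by the print-out would fall wholly in one arm and could not be told apart from an effect of the intervention on severity. The severity-HRQoL relationship could also be affected, because one side of it would be rated by someone who has just read HRQoL scores, again in one arm only.

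**Working it through.** **Step 1: order of events, by arm.**

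| Step | Intervention arm | Control arm |
|---|---|---|
| Before consultation | Skindex-29 completed; print-out to patient and dermatologist | None |
| Consultation | Answers and scores discussed | Usual care, without the Skindex-29 |
| End of consultation | Set of outcome measures | Same set |
| IGA rater | Dermatologist, print-out known | Dermatologist, no print-out |
| PASI rater | Not stated | Not stated |

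The IGA row needs only one inference: that the IGA is completed with the set in which it is listed. The PASI row needs two more: that the treating dermatologist scores it, and does so after seeing the print-out. Neither is written.

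**Step 2: would a shift cancel in change from baseline?** The Skindex-29 is used at all six visits, including baseline, so a shift of constant size would largely cancel. The information is not constant, however. From the second visit the print-out also displays earlier scores, and the scores are expected to change under treatment. Only the part of a shift that differs between baseline and later visits matters for change from baseline.

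**Step 3: precision, from the plan's own figures.** The Power calculation section uses 100 patients per group, a 5% significance level and an autocorrelation of 0.5. It gives no figure for severity, so its primary-outcome figures serve to check the method.

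- SD of change = √(2 × (1 − 0.5)) = 1 baseline SD.
- Standard error of the between-arm difference = 1 × √(2/100) = 0.1414 SD.
- DLQI, difference 1.0 − 0.7 = 0.3 SD: 0.3/0.1414 = 2.121. Two-sided power Φ(2.121 − 1.960) = 56.4% (stated: 56%). One-sided power Φ(2.121 − 1.645) = 68.3% (stated: 68%).
- Communication, difference 0.8 − 0.4 = 0.4 SD: Φ(2.828 − 1.960) = 80.7% (stated: 80%).

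The figures reproduce.

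**Step 4: sensitivity to a rating shift (assumption).** Suppose the same precision holds for a severity rating, patients are independent, and the intervention has no true effect on severity. Let *b* be a pure rating shift, in SD, in the between-arm difference in change. The two-sided rejection rate is 1 − Φ(1.960 − *b*/0.1414) + Φ(−1.960 − *b*/0.1414).

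| Assumed shift *b* | Rejection rate |
|---|---|
| 0 | 5.0% |
| 0.1 SD | 10.9% |
| 0.2 SD | 29.3% |
| 0.3 SD | 56.4% |

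The values of *b* are assumptions. The table shows how sensitive the comparison would be, not how large the bias is.

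**The case against.** **The PASI assessor and the scoring order are not in the text.** This is correct. The end-of-consultation sentence has patients as its subject, and patients do not complete the IGA. The article also refers to separate visit flow charts for each arm (Additional files 1 and 2), which are not shown and may settle the order. The point is therefore firm on who rates the IGA, reasonable on when, and conditional for PASI.

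**Lack of blinding is already acknowledged.** It is, but only as knowledge of the intervention in general. That does not answer an information difference that the visit order can reduce.

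**Scoring first does not restore blinding.** This stands. From the second visit the dermatologist has seen earlier print-outs and discussed them, and is trained and aware of the arm throughout. Only same-day information is removed.

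**The outcome instrument is the DLQI, not the Skindex-29.** This also stands. It means that a direction for any distortion of the severity-HRQoL relationship cannot be asserted.

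**A stronger reading is tempting.** The Participants section says: "Depending on the PASI as measured at week 12 (V3), patients either discontinue treatment in case of PASI <50". A reader might infer that stopping of etanercept is biased by arm and that this carries a quantifiable error into the DLQI comparison. The documents do not support that:

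- The PASI assessor is unknown.
- The dosing schedule is described as a guide, subject to routine practice and the dermatologist's prescription.
- Treatment decisions informed by HRQoL may be part of the effect under test.
- No difference in stopping between arms is given.
- Under the Statistical analysis section, a patient who stops has the last value carried forward, so improvement reached by then is kept.

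**Conclusion.** The concern holds in a limited form. As the article is written, the IGA comes from a dermatologist who has the patient's own symptom and emotion scores in one arm only. The same is true of PASI if that dermatologist scores it after seeing the print-out. This can bias the between-arm comparison of disease severity and the severity-HRQoL relationship.

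It touches one severity measure for certain as regards the rater (IGA) and a second conditionally (PASI). The third, the PGA, is the patient's own rating and is not affected by this route. No size or direction can be derived from the documents, and the rejection rates above depend on assumed shifts. The conclusion assumes that the IGA is completed at the end of the consultation with the rest of the set. Severity is a secondary endpoint, so this is an inexpensive improvement rather than a flaw in the primary comparisons. It makes no claim about stopping or dosing.

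**What to change.** In both arms, have IGA and PASI recorded at the start of the consultation. In the intervention arm, this comes before the Skindex-29 print-out is given to the dermatologist and before HRQoL is discussed. State in the protocol who scores PASI. The patient-completed questionnaires can stay at the end of the consultation, and the intervention itself is unchanged.

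The cost is a small change in visit order and a line in the CRF instructions and the site training. No extra assessor or procedure is needed. The article reports that recruitment is ongoing, so the change should start in both arms together and its date should be recorded. If the visit flow charts already set this order, stating it in the text is enough. The limit of the fix should be stated with it: the rater still knows the arm and the results of previous visits.
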